**Follow-up**

Ongoing attention to participants' posture and exercise adherence after the exercise intervention has ended. A follow-up phone call is made to check the physical status.

**Data management and statistical analysis**

**Preliminary analysis**. Before addressing the main questions of the study, we will examine whether attrition influenced the representativeness of the remaining study sample, whether the intervention conditions were different on demographic variables that are not controlled for in the random assignment procedure, and whether any of the baseline characteristics (e.g., age) need to be accounted for in the primary analyses. Group comparisons on baseline demographic descriptors and primary and secondary outcome measures will be performed using analysis of variance for continuous variables and the chi-square (or Fisher’s Exact) test for categorical variables.

**Main analysis.** To evaluate the effects of PRT on the a priori specified outcomes, a repeated-measures, which will include all assigned participants consistent with the principle of intention-to-treat. The dependent variables will be measures of primary and secondary outcomes collected at baseline, 8 weeks, and 16 weeks, operationalized as continuous variables. Independent variables will be restricted to basic design features: fixed effects for treatment group and time. A one-way analysis of covariance (ANCOVA) taking baseline as the covariance was performed at mid-test and post-test to determine group effects on each outcome parameter.

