**Project summary**

This is a randomized, single-blinded, parallel-controlled, three-group trial. A total of 66 females (mean age 19 years) with poor body posture were recruited from a local university and randomly divided into three groups, Pilates combined with breathing exercise training (PRT) group, Pilates group (PLT), and control group (CON). Randomized participants in each intervention arm will receive a three weekly, 60-minute exercise program for 16 consecutive weeks. Primary and secondary outcome measures will be collected at baseline, 8 weeks, and 16 weeks. An innovative inference reached that PRT can stimulate the diaphragm and strengthen the deep stabilizing muscles and trunk control, the function of the respiratory system may be improved to a certain extent by exercising the core muscles, including the respiratory muscles. It also indirectly affects muscle balance, resulting in improved static postural stability. Thus, the potential mechanism of linkage mechanism shall exsit between respiratory muscles and postural control during Pilates practice that warrants further study. Based on theoretical considerations and previous research on PRT, the overarching working hypothesis is that PRT will show better performance results on primary outcome measures compared to both the PLT training and CON.

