**Recruitment Sources and Procedures**

Potential study participants will be recruited through three major sources: (1) recruitment information posted on WeChat (online) circle of friends; (2) poster campaign; (3) lectures about healthy lifestyle promotion. The study participants will be

recruited from the University in Nanjing. To reduce potential expectation bias, participants will be informed that this study will compare three different groups and that participants will be randomly assigned to either group.

Postural assessments will be conducted by researchers with a professional background in sports human science.

**Baseline Assessments**  Those individuals who are eligible after screening will then be given informed consent materials followed by a baseline evaluation conducted by a study assessor. The baseline assessments will include body mass index (BMI), height, bust circumference, waist circumference, hip circumference, and collection of demographics, health status, and medication use. This will be followed by assessments of lung function, and static posture stability. At that time, the intervention activities involved with the study will be reiterated to the eligible individuals. Those who meet all study criteria, are clear about research procedures, have completed baseline assessments, and give final consent will then be randomized.

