**Randomization and Blinding**

Eligible participants who have signed the informed consent form will be entered into the computer and divided into three equal groups.

All study assessors who will collect study outcome measures will be blinded to study hypotheses and group allocation. Blinding will be strictly maintained by emphasizing to assessors the importance of minimizing assessment bias and regular checking of the blinding status. Participants will be instructed not to reveal their group status to the study assessors at any time.

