**Drop-outs**

Unavoidable drop-outs, such as scheduling conflict, are anticipated. Based on our prior studies involving Pilates, we estimate a 15% dropout rate for the overall study. The proposed sample size will take into account this anticipated dropout rate.

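### Read as written, the repeated-measures model has no group-by-time term, so its group coefficient averages in the pre-randomisation visit, and the plan does not rank it against the valid ANCOVA beside it

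*Protocol*

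**What the plan says.** All of this stands in the protocol under Data management and statistical analysis, in the paragraph headed Main analysis.

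- **Purpose.** The paragraph opens "To evaluate the effects of PRT on the a priori specified outcomes, a repeated-measures"; the noun for the model is missing. The analysis is to include everyone assigned, on the intention-to-treat principle.
- **Outcomes.** "The dependent variables will be measures of primary and secondary outcomes collected at baseline, 8 weeks, and 16 weeks".
- **Model terms.** "Independent variables will be restricted to basic design features: fixed effects for treatment group and time". No group-by-time interaction is named here or elsewhere in the protocol.
- **Second analysis.** The next sentence reads "A one-way analysis of covariance (ANCOVA) taking baseline as the covariance was performed at mid-test and post-test to determine group effects". It covers each outcome parameter.

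Nothing states which of the two analyses carries the conclusion. Under Recruitment Sources and Procedures, baseline comes before allocation: those who "have completed baseline assessments, and give final consent will then be randomized".

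**The concern.** The hypothesis in the Project summary is that Pilates plus breathing training (PRT) does better than Pilates alone (PLT) and control (CON). With a pre-treatment visit in the outcome vector, that question is about differential change: how far the arms separate after baseline. A model with only main effects for group and time has no parameter for this. Its time term is shared by all arms, and its group term assumes the same difference at every visit, baseline included.

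At stake is how the trial will be read. The repeated-measures model comes first and is the one tied to intention-to-treat. If its group term is reported as the effect of PRT, a real effect is understated and may be declared absent. The ANCOVA on the same data could be clearly positive. With no ranking, the choice between them could be made after the results are seen.

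**Working it through.** The protocol gives no effect size, SD, correlation, alpha or power, so it has no figure to reproduce. The dilution follows from the model; the power figures are illustrations under stated assumptions.

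**Inputs from the protocol**
- Three visits in the outcome vector, and fixed effects for group and time only (Main analysis).
- Baseline measured before randomisation, so the expected group difference there is 0.
- "A total of 66 females (mean age 19 years) with poor body posture were recruited" (Project summary) and "divided into three equal groups" (Randomization and Blinding): 66/3 = 22 per arm.
- "we estimate a 15% dropout rate for the overall study" (Drop-outs): 66 × 0.85 = 56.1, or 18.7 per arm, taken as 19.

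**Step 1: what the group coefficient estimates.** Let d8 and d16 be the true differences between two arms at weeks 8 and 16. The additive model fits one difference to the visit differences (0, d8, d16). With complete data it is their weighted mean, with weights V⁻¹1 / (1′V⁻¹1), where V is the covariance of the three visits.

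**Step 2: compound symmetry.** The weights are 1/3 each at any correlation, so the coefficient estimates (0 + d8 + d16)/3.
- d8 = d16: (0 + 1 + 1)/3 = 67% of the week-16 effect.
- d8 half of d16: (0 + 0.5 + 1)/3 = 50%.
- d8 = 0: (0 + 0 + 1)/3 = 33%.

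**Step 3: another covariance.** Under AR(1) with correlation 0.3 to 0.9 the baseline weight is 0.37 to 0.48.
- d8 = d16: 63% down to 52%.
- d8 half of d16: 50% throughout.
- d8 = 0: 37% up to 48%.

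The exact ratio depends on the covariance, but dilution remains in every case examined.

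**Step 4: simulation check.** With 5000 runs, 22 per arm, correlation 0.7 and a true effect of 0.80 SD at both visits, the mean group coefficient was 0.53. The week-16 ANCOVA and the group-by-time contrast at week 16 both averaged 0.80.

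**Step 5: illustrative power.** Assume 0.8 SD at both visits, correlation ρ = 0.7, compound symmetry, one pairwise comparison, two-sided 5%, noncentral t.

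- Group term: estimate (0 + 0.8 + 0.8)/3 = 0.533; SE = √(2 × ((1 + 2ρ)/3)/n) = √(2 × 0.8/n).
- Week-16 ANCOVA: estimate 0.8; SE = √(2 × (1 − ρ²)/n) = √(2 × 0.51/n).

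| Per arm | Group term: SE, estimate/SE, power | Week-16 ANCOVA: SE, estimate/SE, power |
|---|---|---|
| 19 | 0.290, 1.84, 43% | 0.232, 3.45, 92% |
| 22 | 0.270, 1.98, 49% | 0.215, 3.72, 95% |

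With 0.4 SD at week 8 and 0.8 SD at week 16, 19 per arm and ρ = 0.7, the group term has 27% and the ANCOVA still 92%. Over ρ = 0.5 to 0.8 and both effect patterns at 19 per arm, the ranges are 25–50% and 79–98%. The choice of degrees of freedom, or a normal approximation, moves these by about one or two points.

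**Step 6: under no effect.** If d8 = d16 = 0, the coefficient has expectation zero and its test is not inflated. Chance baseline imbalance adds variance to the estimate, not bias.

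**The case against.** The strongest objection is that the paragraph already contains a sound answer. The ANCOVA compares the arms at weeks 8 and 16 with adjustment for baseline, and it is the analysis given the task of determining group effects. A reader might infer from the repeated-measures sentence that the main analysis as a whole is biased, or that the trial cannot estimate its treatment effect. The protocol does not support that. For the same reason, the power gap above lies between two analyses that are both planned; it is not power lost to the trial. This stands, and it limits the point to one model and the missing ranking.

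The second objection is about wording. The preceding paragraph asks whether baseline characteristics need to enter the primary analyses, so the restriction to design features may only mean that no extra covariates are added. The sentence is visibly loose, and the author may have meant a factorial model with its interaction. That is possible, so one cannot be sure that the interaction is deliberately excluded. But the text presents a closed list without it, and if the interaction is intended, the sentence still needs the same correction.

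Third, the power figures rest on an assumed effect and correlation, and 19 per arm is a completer count, whereas the model is meant to include all assigned. That is fair, and figures at 22 are therefore shown as well. The dilution itself needs no effect size, only an assumed pattern over visits and a covariance.

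**Conclusion.** The point holds for the repeated-measures model as written. Its group coefficient mixes in a visit at which no treatment effect can exist. Under compound symmetry with complete data it is 67%, 50% or 33% of the week-16 effect for the three patterns above; under AR(1) it is between 37% and 63%. The consequence is attenuation and loss of power in that model. Inflated type I error is not a consequence.

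The ANCOVA is valid and estimates the treatment effect, so the trial is not left without an answer. What remains is that one of two main analyses does not address the hypothesis and that nothing says which of them decides. A diluted null result and a positive ANCOVA could both be reported as the main result. For illustration only, 0.8 SD at both visits and correlation 0.7 give about 43% against 92% at 19 per arm, and about 49% against 95% at 22.

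**What to change.** In the Main analysis paragraph:

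1. Delete the phrase that restricts the independent variables, and add the group-by-visit term.
2. Handle baseline in one of two ways: as a covariate with weeks 8 and 16 as the outcomes, or within the outcome vector with its mean constrained to be common to the three arms.
3. Name the week-16 PRT–PLT and PRT–CON contrasts as the treatment effects. Week 16 is the end of the intervention under Outcome Measure.
4. State whether this model or the ANCOVA is primary, and give the other a supporting role.

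The covariance structure can be left to the SAP. The cost is one or two sentences and a change to the model code; no new data are needed.

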**Intervention Instructors**

The PRT was conducted at 16:00-18:00 on Monday, Wednesday and Friday, whereas PLT was conducted at the same time slots on Tuesday, Thursday and Saturday. One qualified Pilate instructor trained the two groups in the same gym hall to ensure that the participants in the two exercise groups received the same training guidance.

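### The exercise arms are taught as classes in separate timetables, but the outcome analyses treat participants as independent: with one class of 22 per arm and an assumed class ICC of 0.05, type I error is about 17% for PRT versus PLT and 11–12% for PRT versus CON

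*Protocol*

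**What the plan says.** **Allocation.** The Protocol's Project summary gives the size: "A total of 66 females (mean age 19 years) with poor body posture were recruited". Under Randomization and Blinding, participants are "divided into three equal groups", which is 22 per arm.

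**Delivery.** The Intervention Instructors section sets the timetable for each exercise arm: "The PRT was conducted at 16:00-18:00 on Monday, Wednesday and Friday, whereas PLT was conducted at the same time slots on Tuesday, Thursday and Saturday". On staffing and venue, the same section says: "One qualified Pilate instructor trained the two groups in the same gym hall". The Class Location section has weeks 1–8 supervised in a gym and weeks 9–16 done online from home. The sections on adherence, safety and quality assurance all speak of classes and class attendance. No class is described for CON.

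**Analysis.** Under Data management and statistical analysis, the repeated-measures analysis is limited as follows: "Independent variables will be restricted to basic design features: fixed effects for treatment group and time". The second analysis reads: "A one-way analysis of covariance (ANCOVA) taking baseline as the covariance was performed at mid-test and post-test to determine group effects on each outcome parameter". Neither mentions class membership, an ICC or a design effect.

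**The concern.** This is an individually randomised trial with group-delivered treatment in two of its three arms. People who train together three times a week share whatever is particular to their class, so their outcomes may be correlated. CON members share nothing comparable. The design is therefore partially nested.

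The planned tests judge an arm difference against variation between individuals only. Any variation between classes is left out of the error term but remains in the arm means. If each exercise arm is one class, class and arm coincide completely. A chance difference between the two classes then cannot be told apart from an effect of the breathing training.

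The working hypothesis is that PRT does better than both PLT and CON, so both contrasts matter. PRT versus PLT matters most, because it is the only one that isolates the breathing component, and it has a class effect on both sides.

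**Working it through.** **Inputs from the Protocol**
- 66 participants in three equal groups: 66 / 3 = 22 per arm.
- Drop-out 15% (Drop-outs section): 22 × 0.85 = 18.7, about 19 per arm.
- Sessions of 60 minutes (Duration of the project) in a two-hour slot (Intervention Instructors). The number of classes per arm is not stated.

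**Assumptions, not in the Protocol**
- Two-sided 5% level.
- Class ICC ρ of 0.05 on the baseline-adjusted outcome, with a range of 0.01–0.10.
- No class effect in CON, and no true treatment effect.

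The Protocol has no figure of its own on this point to reproduce beyond 22 per arm.

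**Step 1: design effect.** For class size m, DE = 1 + (m − 1)ρ. With m = 22 and ρ = 0.05, DE = 1 + 21 × 0.05 = 2.05. The effective size of an exercise arm is 22 / 2.05 = 10.7. In CON, DE = 1.

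**Step 2: standard-error multiplier.** For two arms of equal size it is √((DE₁ + DE₂)/2).
- PRT–PLT: √2.05 = 1.43.
- PRT–CON: √((2.05 + 1)/2) = √1.525 = 1.235, about 1.24.

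**Step 3: actual type I error** = 2[1 − Φ(1.96 / multiplier)].
- PRT–PLT: 1.96 / 1.43 = 1.37, giving 17.1%.
- PRT–CON: 1.96 / 1.235 = 1.59, giving 11.2%.

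**Step 4: check by simulation.** The three-group ANCOVA was simulated under the null in two separate sets, of 20,000 and 40,000 trials per setting. The ICC 0.01 row has the 20,000-trial set only. One class of 22 per exercise arm:

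| ICC | DE | PRT–PLT, formula | PRT–PLT, simulated | PRT–CON, formula | PRT–CON, simulated | Three-group test, simulated |
|---|---|---|---|---|---|---|
| 0 | 1.00 | 5.0% | 5.0–5.2% | 5.0% | 5.0–5.1% | 5.1% |
| 0.01 | 1.21 | 7.5% | 7.5% | 6.2% | 6.1% | 7.1% |
| 0.02 | 1.42 | 10.0% | 9.7–10.0% | 7.5% | 7.4–7.6% | 9.4% |
| 0.05 | 2.05 | 17.1% | 17.2–17.4% | 11.2% | 11.5–11.9% | 17.2–17.6% |
| 0.10 | 3.10 | 26.6% | 27.0–27.7% | 17.1% | 17.7–18.1% | 29.3–29.4% |

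**Step 5: other class sizes at ICC 0.05**
- About 19 per arm, one class: DE = 1 + 18 × 0.05 = 1.90. PRT–PLT 15.5%, PRT–CON 10.4% (formula); three-group test 15.3% (simulated).
- Two classes of 11 per arm: DE = 1 + 10 × 0.05 = 1.50. PRT–PLT 11.0%, PRT–CON 8.0% (formula).

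**Step 6: price of the correction.** A PRT–PLT contrast with 80% power under independence has an expected z of 1.96 + 0.84 = 2.80. Dividing by 1.43 gives 1.96, so power falls to about 50% if the ICC really is judged at 0.05.

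Only the single-time ANCOVA was simulated. The repeated-measures analysis omits class in the same way, but the size of the effect there was not calculated.

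**The case against.** **The ICC is unknown and may be small.** This stands. The outcomes are spirometry and photographic or tape measurements. The two exercise arms share an instructor and a hall, a uniform intervention protocol applies, and weeks 9–16 are done from home, so the week-16 outcome follows eight weeks away from the gym. All this favours the lower end of the range. It does not bring the ICC to zero, and the week-8 analysis comes straight after the supervised phase.

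**One class of 22 is not stated.** This also stands. A 60-minute session in a two-hour slot leaves room for two sittings per arm, which lowers the inflation but does not remove it.

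**The model sentence restricts fixed effects, so a random class term could still appear in an analysis plan that is not shown.** This is partly right: the sentence does not strictly forbid such a term. But the Protocol does fix the terms of its model and names a one-way ANCOVA on baseline. With one class per arm, no model term could separate class from arm in any case.

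**Inference may be meant only for the programmes as delivered to these groups.** On that target, individual randomisation supports the independence-based comparison. That is a legitimate choice, but the Protocol does not make it, and attributing a PRT–PLT difference to breathing training goes beyond it.

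**Stronger readings.** A reader might infer that the error rate is tripled for PRT in general. It is not: PRT–CON is only about doubled, because CON has no class. A reader might also infer that every planned test is affected. The baseline comparisons precede any class exposure and are sound in this respect.

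**Conclusion.** The point holds as a conditional one. The Protocol describes class delivery in two arms and analyses outcomes as if participants were independent, so the arm contrasts are anti-conservative under any positive class ICC when inference is meant to reach beyond the particular classes run.

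With one class of 22 per exercise arm, an assumed ICC of 0.05 and a two-sided 5% level, type I error is about three times nominal for PRT–PLT and the three-group test (about 17%), and about twice nominal for PRT–CON (11–12%). Over ICC 0.01–0.10 the ranges are about 7.5–27% and 6–18%. Two classes of 11 per arm at ICC 0.05 give about 11% and 8%.

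The documents do not establish where in that range the trial lies. They also do not support making an assumed ICC of 0.05 the gate for claiming superiority: the data cannot estimate it with one class per arm, and the power loss would be large. What they do support is showing how far each conclusion depends on the ICC.

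**What to change.** In Data management and statistical analysis:

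1. Record class membership for every PRT and PLT participant, and state how many classes each arm had.
2. Keep the planned ANCOVA. Alongside it, report PRT–PLT and PRT–CON at weeks 8 and 16 with standard errors inflated for class in the exercise arms only, over ICC 0.01–0.10, using the class size actually analysed. At 22 per class and ICC 0.05 the multipliers are about 1.43 and 1.24.
3. State the ICC at which each contrast loses significance. With r the ratio of the observed t to its critical value, this is (r² − 1)/(m − 1) for PRT–PLT and 2(r² − 1)/(m − 1) for PRT–CON.
4. If only one class per arm was run, state that class is confounded with arm, that the PRT–PLT result is conditional on those two classes, and that it is not by itself attributed to the breathing training.
5. If several classes per arm were run, add as a sensitivity analysis a partially nested model with a class random effect in PRT and PLT and small-sample degrees of freedom. Note how few class-level degrees of freedom there are: with two classes per arm, PRT–PLT has 4 − 2 = 2.

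The cost is a few lines of wording and analysis, with no added participants or visits. The downside is wider reported intervals and a more cautious conclusion, chiefly for PRT–PLT.

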**Class Location**

The first eight weeks involved supervised exercise at a gym, followed by eight weeks (weeks 9-16) of home-based online training.

**Intervention Adherence**  Every participant is expected to commit to a four-month period of intervention. Attendees will be motivated to join every session of the intervention (totaling 48), anticipating a compliance rate exceeding 85%. A research assistant will meticulously track class participation every two weeks in the initial month, followed by monthly checks thereafter. Individuals will be classified as drop-outs if they discontinue participation in the intervention, do not come back for assessments, or are absent for over four weeks in a row during their designated intervention. Every participant ceasing participation in the intervention sessions will be promptly reached out to and urged to come back for all assessments. Every participant who dropped out will be subjected to an exit interview to ascertain their reasons for discontinuing the study.

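### The protocol names two unranked main analyses that estimate different effects, and ties the all-assigned population only to the first

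*Protocol*

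**What the plan says.** Protocol, Data management and statistical analysis, Main analysis. One paragraph holds two analyses.

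- The first is a repeated-measures analysis (the noun naming the model is missing), "which will include all assigned participants consistent with the principle of intention-to-treat". Its dependent values are the outcomes at baseline, 8 weeks and 16 weeks. Its independent variables are limited to group and time.
- The second reads: "A one-way analysis of covariance (ANCOVA) taking baseline as the covariance was performed at mid-test and post-test". Its stated purpose is to find the group effect on each outcome. No population and no handling of missing values is given for it.

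Nothing says which of the two decides the trial.

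On loss, the section Drop-outs says "we estimate a 15% dropout rate for the overall study", with no split by arm. The one reason given is an example: "Unavoidable drop-outs, such as scheduling conflict, are anticipated". Intervention Adherence, under Class Location, counts as drop-outs people who "discontinue participation in the intervention, do not come back for assessments, or are absent for over four weeks in a row" from their assigned intervention. It adds that those who stop are contacted and urged to attend all assessments. The preliminary analysis will look at whether attrition affected representativeness.

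**The concern.** Both analyses are meant to deliver the treatment effect, and they can disagree. If they do, the protocol gives no rule for which to believe, so the choice can be made once the results are known. The ANCOVA is also run at two visits, with neither named as decisive.

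The intention-to-treat commitment belongs grammatically to the repeated-measures sentence alone. If the conclusion ends up resting on the ANCOVA, nothing in the text secures that everyone randomised is in it. Without imputation, an ANCOVA at week 16 omits people with no week-16 value and makes no use of their week-8 value.

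The drop-out definition adds uncertainty. It puts stopping or missing the intervention, which is non-adherence, under the same label as not returning for assessment, which means a missing outcome.

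**Working it through.** **1. What each analysis estimates.** Let d0, d8 and d16 be the group differences at the three visits. With group and time only, complete data and equal correlation between visits, the group term is the plain average:

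group term = (d0 + d8 + d16) / 3

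Randomisation makes d0 zero in expectation. For an assumed steady effect of 0.5 SD:

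- repeated measures: (0 + 0.5 + 0.5) / 3 = 0.33 SD
- ANCOVA: 0.5 SD at each later visit

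Other correlation patterns change the weights. Baseline is still one of the values being averaged.

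**2. How many could leave the week-16 ANCOVA.** The inputs are from the protocol: 66 participants (Project summary), three equal groups (Randomization and Blinding) and 15% drop-out (Drop-outs).

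- lost: 66 × 0.15 = 9.9, about 10
- remaining: 66 × 0.85 = 56.1, or 56.1 / 3 = 18.7 of 22 per arm

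At the protocol's own rate this is an upper bound, because some people labelled drop-outs will still be assessed. The figure of 66 itself cannot be reproduced: the protocol gives no alpha, power, effect size or SD with it.

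**3. Whether such loss biases the ANCOVA, and in which direction.** As a bounding case, suppose the worst 15% of one arm on a normal outcome are lost. That arm's mean then shifts by φ(z₀.₁₅) / 0.85 = 0.27 SD. If both arms lose the same share in the same way, the shifts cancel.

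A simulation covers less extreme cases. Its assumptions, none from the protocol, are: two arms of 22, correlation 0.7 between visits, true effect 0.5 SD, about 15% lost overall at week 16, poor responders lost first (with noise added), and 4,000 runs per setting. Everyone has a week-8 value. The likelihood-type estimate combines two regressions:

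- week 8 on baseline and group, in everyone, giving group coefficient β
- week 16 on baseline, group and week 8, in completers, giving group coefficient γ and week-8 coefficient λ
- effect at week 16 = γ + λβ

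Bias in SD units:

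| Loss, PRT / comparator | ANCOVA, loss by week-8 change | Likelihood, same | ANCOVA, loss by unseen week-16 change | Likelihood, same |
|---|---|---|---|---|
| 15% / 15% | 0.00 | 0.00 | 0.00 | 0.00 |
| 30% / 0% | +0.11 | 0.00 | +0.27 | +0.23 |
| 0% / 30% | −0.12 | −0.01 | −0.27 | −0.23 |
| 20% / 10% | +0.03 | 0.00 | +0.09 | +0.08 |
| 10% / 20% | −0.03 | 0.00 | −0.09 | −0.08 |

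When loss is unrelated to response, both methods are within 0.003 SD of the truth at every split. The sign of the bias follows which arm loses more poor responders. The likelihood approach removes the bias when loss depends on observed week-8 values, and only a small part of it when loss depends on the unseen value.

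**The case against.** A reader might infer that the ANCOVA is a completers-only analysis, so that intention-to-treat is not delivered. The protocol does not say so. Omission of people without an outcome is what happens if nothing is imputed, and a missing-data rule may stand in a statistical analysis plan that is not shown. What stands is that the protocol does not assure intention-to-treat for this analysis.

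A reader might also infer that the effect is biased upward, since only the exercise arms carry 48 sessions. That is not supported. Drop-out is given for the study as a whole, and the one reason named has no link to response. Equal loss gives no bias, and greater loss in the comparator reverses it. The session argument does not reach PRT against PLT at all, because those arms have the same session length and frequency.

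A third tempting reading is that the drop-out label removes non-attenders, and does so differently by arm because no classes are described for control. The label does fit the control arm poorly. But no text excludes drop-outs from analysis: the label leads to contact, a request to return and an exit interview.

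The change of tense between the two sentences proves nothing, since the protocol mixes tenses throughout. It may also be that a group-by-time term was intended, but the listed effects do not include one.

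None of this ranks the two analyses. That defect lies in what the protocol states, not in detail left to a later document.

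**Conclusion.** The point holds as a problem of unranked and differing main analyses. It does not hold as a demonstrated bias.

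From the text alone: two analyses share one Main analysis heading, they estimate different quantities, and the all-assigned wording covers only the first. The illustration of 0.33 against 0.5 SD rests on a steady effect, equal correlations, complete data and no group-by-time term.

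From arithmetic on the protocol's figures: at most about 10 of 66 would be absent from an unimputed week-16 ANCOVA at the expected drop-out rate.

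From assumptions only: the bias ranges from about −0.27 to +0.27 SD across the splits tried, and is zero when loss is equal. The loss rates by arm, the correlation and the loss mechanism are not in the protocol, so neither a size nor a direction can be claimed for this trial. The matter should be settled in writing before outcome data are compared by group.

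**What to change.** - Name one main analysis: a likelihood-based repeated-measures model of the week-8 and week-16 values, with baseline as covariate and group, visit and group-by-visit as fixed effects. Use every available value from every randomised participant, regardless of attendance.
- Name the contrast and the visit that decide the trial.
- Keep the visit-wise ANCOVA as a sensitivity analysis, stating its population and how missing values are handled.
- State that the model removes bias only when loss depends on observed values, and that someone with neither later visit adds no outcome information. Report the number of such people by arm.
- Under Intervention Adherence, record stopping the intervention separately from being lost to assessment, and state that people who only stop the intervention stay in the analysis.

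The cost is protocol wording and slightly more modelling work. No new data are needed, since the visits are already planned and people who stop are already asked to return for them.
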